### Participants

Sample size for the group phase was set to *N* = 120 (*n* = 40 per condition). A minimum of *n* = 90 individuals (*n* = 30 per condition) is expected to complete individual CBT. Targeted sample sizes are based on power calculations. The intended sample of 120 individuals can be expected to provide sufficient power to detect small effects [67].

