### Assessments

Participants will be assessed at intake and at 10 points over the course of the study: before (T1), during (T2-4), and after the group-based phase (T5), after the subsequent 4-week follow-up waiting phase before individual CBT starts (T6), during (T7-9), and post the first four months of individual CBT (T10). Measures will include self-report questionnaires, interviews, observer-based ratings, EMA, experimental investigations, and analyses of hair steroids. Questionnaires will all be provided in paper pencil format and in German language. Interviews will be conducted face-to-face by intensively trained Master’s students majoring in clinical psychology who will closely be supervised by psychotherapists and psychotherapists in training for CBT, all of whom have Master’s degrees in clinical psychology. Participants will be provided with iPhones for the EMA. Over 7-day periods, time-contingent assessments will be taken 3 times per day and one hour after each of the three assessments. Participants will be given the chance to supplement time-contingent assessments with event-contingent assessments whenever they feel significantly distressed. Enrolled patients will also be asked to participate in an experimental investigation of ER skills and to provide hair probes. Participants will be compensated 50 Euros for the burden associated with study diagnostics, and an additional 20 Euros will be provided for participating in the experiment or providing hair probes. An overview of study variables, assessment points, and instruments is provided in Table 1.

**Table 1 T1:** Overview of study variables and instruments

**Domain**	**Instrument**	**T0**	**T1**	**T2**	**T3**	**T4**	**T5**	**T6**	**T7**	**T8**	**T9**	**T10**
Depressive symptom severity (primary outcome)	Hamilton rating scale for depression		✕		✕			✕				✕
Diagnostics	Structured clinical interview for DSM-IV Axis I, II	✕						✕				✕
Stressors	List of situational stressors		✕	✕	✕	✕	✕	✕	✕	✕	✕	✕
Additional indicators of mental health	Beck depression inventory II		✕	✕	✕	✕	✕	✕	✕	✕	✕	✕
	Scales of psychological well-being		✕	✕	✕	✕	✕	✕	✕	✕	✕	✕
	Pos. and neg. affect schedule		✕	✕	✕	✕	✕	✕	✕	✕	✕	✕
	Short scales of affective states relevant for psychotherapy		✕	✕	✕	✕	✕	✕	✕	✕	✕	✕
	SHARP/others		✕				✕	✕				✕
	Brief symptom inventory		✕				✕	✕				✕
	Depression anxiety and stress scale		✕	✕	✕	✕	✕	✕	✕	✕	✕	✕
Emotion regulation	Emotion reg. skills questionnaire		✕	✕	✕	✕	✕	✕	✕	✕	✕	✕
	ERSQ- others		✕				✕	✕				✕

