### Statistical analyses

Data will be analyzed according to intent to treat and treatment completers principles. The intent to treatment analyses will be the primary level of analyses. Mixed effect modeling will serve as the main approach in the analyses of study data and in the treatment of missing values.

Growth curves of ER and depressive symptom severity will be computed per group on the basis of assessments before (T1-T5) and during individual CBT (T6-T10) to test for stand-alone and augmentation effects of ART. Slopes for the ART condition are hypothesized to be larger than those for the active or waitlist control groups, indicating the effectiveness of adaptive ER skills application enhancement and a decrease in depressive symptom severity by the ART program. In the secondary analyses, we will test for ART effects on well-being, positive, and negative affect. Bootstrapping enhanced, multilevel mediation analyses [68] will be conducted to test ER as a mediator of health improvements in the ART condition. Analyses will be conducted computing a total score of adaptive ER and separately for the different ART skills to understand the importance of specific ER skills. Moderated mediation analyses [69] will be used to examine the importance of specific ER skills in the mediation of positive health outcomes. Latent growth curve and latent change score modeling [70] will further be used in the investigation of reciprocal associations between levels and changes of ER and health outcomes. Comorbid symptom severity and potential confounding variables (i.e., general self-efficacy, perfectionism, and self-esteem) will be included in the analyses as moderating variables. The analyses of EMA and the experimental and biological data will serve to increase the validity of the ART evaluation. SEM-based Multi-Trait, Multi-Method approaches will be applied in the investigation of psychometric properties and in the comparison of outcomes by different assessment methods.

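### The claim that 120 patients give sufficient power for small effects is not met for the pairwise ART-versus-control contrasts that the trial sets out to test

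*Protocol article*

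**What the plan says.** The Participants section sets 40 patients per arm for the group phase and adds: "A minimum of *n* = 90 individuals (*n* = 30 per condition) is expected to complete individual CBT". It then says "Targeted sample sizes are based on power calculations" and concludes: "The intended sample of 120 individuals can be expected to provide sufficient power to detect small effects". It gives no alpha, sidedness, target power, effect metric or correlation between repeated measurements.

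The Statistical analyses section states the comparison of interest: "Slopes for the ART condition are hypothesized to be larger than those for the active or waitlist control groups". The method is given as "Mixed effect modeling will serve as the main approach in the analyses of study data and in the treatment of missing values", with separate growth curves for T1–T5 and T6–T10, and intention to treat as the primary level of analysis. In Table 1 the row "Hamilton rating scale for depression", which is the primary outcome, is marked at T1, T3, T6 and T10. Each analysed phase therefore contains two ratings.

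**The concern.** An article may leave the inputs of a power calculation to a fuller document. Here, however, it states the conclusion as a property of the design. ART is compared with the active control and with the waitlist, so each contrast rests on 80 patients. That number is usually associated with medium to large standardised differences.

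The comparison with the common-factor control matters most, because it isolates what ART adds beyond non-specific therapy, and a modest difference is plausible there. A reader who accepts the power statement could take a non-significant result as evidence against even a small benefit, when the design would often miss considerably larger ones. The same applies to the question of whether ART augments individual CBT.

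**Working it through.** The article gives no numerical power, so there is no figure to reproduce. What can be tested is whether the verbal claim holds under any reasonable reading.

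**Inputs from the article.** Three arms of 40; at least 30 per arm completing individual CBT; pairwise ART-versus-control hypotheses; two Hamilton ratings per phase (Table 1).

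**Assumptions, none stated in the article.** Two-sided alpha 0.05; 80% as sufficient power; small = d 0.2 for two arms or f 0.10 for three; correlation ρ varied.

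**1. Unadjusted comparison at one time point.** Noncentral t with noncentrality d√(n/2):
- n = 40: 0.2 × √20 = 0.894, 78 df, power 14.3%.
- n = 30 (completers): 0.2 × √15 = 0.775, 58 df, power 11.9%.
- 80% power at d = 0.2 needs 394 per arm, about ten times the planned 40.

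**2. Baseline adjustment.** The residual SD shrinks by √(1 − ρ²), so the effective d is 0.2/√(1 − ρ²).

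| ρ | effective d | power, n = 40 | power, n = 30 |
|---|---|---|---|
| 0.5 | 0.231 | 18% | 14% |
| 0.7 | 0.280 | 24% | 19% |
| 0.8 | 0.333 | 31% | 25% |
| 0.9 | 0.459 | 53% | 42% |

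**3. Other variants at d = 0.2.**
- A linear slope contrast over five assessments, with no random slope (a favourable assumption), gives 17%, 25%, 35% and 61% at 40 per arm for ρ = 0.5, 0.7, 0.8 and 0.9.
- ART against the pooled controls (40 against 80), unadjusted, gives 18%.
- A one-sided test with baseline adjustment at ρ = 0.9 gives about 66%.

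None of these reaches 80%.

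**4. Small read as f = 0.10.** A three-arm F test at one time point gives 14.8% at N = 120. For an omnibus group-by-time interaction with m assessments, λ = f²·N·m/(1 − ρ). With m = 2 and N = 120, λ = 0.01 × 120 × 2/(1 − ρ) = 2.4/(1 − ρ), on 2 and 117 df:
- ρ = 0.5: λ = 4.8, power 48%.
- ρ = 0.7: λ = 8.0, power 71%.
- ρ = 0.8: λ = 12.0, power 87%.

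**5. What f = 0.10 means with two ratings.** The interaction effect in each cell is half the deviation of that arm's mean change from the overall mean change. So f = 0.10 means that the arms' mean changes have a standard deviation of 2 × 0.10 = 0.20 outcome SD.
- If one arm of three differs by δ, that standard deviation is δ√(2/9), so δ = 0.20/0.471 = 0.42 SD.
- If the arms are equally spaced with range δ, it is δ/√6, so δ = 0.20 × 2.449 = 0.49 SD.

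**6. Detectable pairwise d at 80% power.**
- 40 per arm: 0.634 unadjusted; × 0.866 = 0.55 at ρ = 0.5; × 0.714 = 0.45 at ρ = 0.7.
- 30 per arm: 0.736 unadjusted; 0.64 at ρ = 0.5; 0.53 at ρ = 0.7.

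**The case against.** The strongest defence is that small has no metric in the article, and that N = 120 does deliver adequate power on one conventional reading. For an f = 0.10 omnibus interaction with five assessments, power is 68%, 79% and 91% at ρ = 0.5, 0.6 and 0.7. The abstract says that all outcomes are measured at every time point, and the BDI-II is taken at all of T1 to T10. That stands as far as it goes: the authors have not been shown to have miscalculated, since no figure is given. It does not rescue the claim for the primary outcome, because Table 1 as it reads gives the Hamilton scale two points per phase, and an omnibus test is not the pairwise hypothesis. If the table has been damaged in extraction and five ratings exist, the omnibus reading becomes attainable, but pairwise power at d = 0.2 still reaches only 61% at ρ = 0.9.

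Three stronger readings are tempting, and the article does not support them:
- **That the trial's power is 12–15%.** Those figures belong to an unadjusted test at one time point. The planned analysis is a mixed model, whose power at d = 0.2 depends on the correlation and the number of assessments.
- **That the augmentation question has only 12% power.** Thirty per arm is the expected number of completers. Intention to treat is primary and mixed models handle missing values, so 30 per arm is a sensitivity case. The power sentence itself refers only to the 120.
- **That clustering within therapy groups was left out of the calculation.** The calculation is not displayed, so this cannot be shown either way.

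**Conclusion.** The point stands in limited form. For the pairwise contrasts that the article hypothesises, sufficient power for small effects is not delivered at 40 per arm. At d = 0.2 and two-sided alpha 0.05, power is about 14% unadjusted and 18% to 53% with a baseline correlation of 0.5 to 0.9, and no variant tried reaches 80%. The one reading that can satisfy the sentence uses a different test, needs a correlation of about 0.8 with two Hamilton ratings per phase, and treats a difference in change of 0.42 to 0.49 SD as small. All of this rests on the assumed d, alpha and 80% target. The direction of the conclusion does not depend on which analysis model or correlation in the range is chosen.

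**What to change.** In Participants, delete the reference to small effects and state what the design can detect, with the assumptions. For example: at 80% power and two-sided alpha 0.05, 40 per arm detects a pairwise difference of about d = 0.63 (0.55 with baseline correlation 0.5, 0.45 with 0.7); a completer analysis at 30 per arm detects about 0.74 (0.64 and 0.53).

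Name the effect metric, the assumed correlation and the number of Hamilton assessments used. Add that smaller differences will be reported as estimates with confidence intervals and not as absence of effect.

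The cost is a few lines of text and a less favourable stated figure. Enrolment and the planned analysis do not change.

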### Statistical analyses

Data will be analyzed according to intent to treat and treatment completers principles. The intent to treatment analyses will be the primary level of analyses. Mixed effect modeling will serve as the main approach in the analyses of study data and in the treatment of missing values.

Growth curves of ER and depressive symptom severity will be computed per group on the basis of assessments before (T1-T5) and during individual CBT (T6-T10) to test for stand-alone and augmentation effects of ART. Slopes for the ART condition are hypothesized to be larger than those for the active or waitlist control groups, indicating the effectiveness of adaptive ER skills application enhancement and a decrease in depressive symptom severity by the ART program. In the secondary analyses, we will test for ART effects on well-being, positive, and negative affect. Bootstrapping enhanced, multilevel mediation analyses [68] will be conducted to test ER as a mediator of health improvements in the ART condition. Analyses will be conducted computing a total score of adaptive ER and separately for the different ART skills to understand the importance of specific ER skills. Moderated mediation analyses [69] will be used to examine the importance of specific ER skills in the mediation of positive health outcomes. Latent growth curve and latent change score modeling [70] will further be used in the investigation of reciprocal associations between levels and changes of ER and health outcomes. Comorbid symptom severity and potential confounding variables (i.e., general self-efficacy, perfectionism, and self-esteem) will be included in the analyses as moderating variables. The analyses of EMA and the experimental and biological data will serve to increase the validity of the ART evaluation. SEM-based Multi-Trait, Multi-Method approaches will be applied in the investigation of psychometric properties and in the comparison of outcomes by different assessment methods.

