## Methods/Design

The study is designed as a prospective randomized controlled trial in an outpatient setting. Following three sessions with their individual therapists, enrolled patients will be assigned to the ART group, an active common factor-based treatment control condition (CFT-C) or a waitlist control group using a computerized randomization tool (randomisation.net). Group therapies will be provided for 18 hours over the course of 8 weeks. Participants in the waiting condition will be offered to participate in ART after completion of the study. Following the group and a 4-week follow-up waiting phase, all participants will receive 16 hours of standardized and manualized iCBT for depression. Individual treatment will be continued beyond the study if necessary. An overview of the study design is illustrated in Figure 1. The study has been approved by the ethical committee of the German Psychological Society and of the University of Marburg. It was registered with ClinicalTrials.gov, number NCT01330485.

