### Recruitment

Study participants will be recruited at outpatient treatment centers in Marburg, Mainz, and Kassel. Potential participants will be screened on eligibility and provided with study information on the phone. Interested and potentially eligible patients will receive additional written information on the study and be invited to a Structured Clinical Interview for DSM-IV Axis I and II (SCID I, II) in one of the study centers. Patients meeting inclusion criteria and having provided informed consent will be included in the study. Recruitment will be conducted consecutively, that is, 10 to 15 individuals at a time will be enrolled in each cohort.

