### Interventions

Interventions will include ART and CFT-C as group interventions and individual CBT for MDD.

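### ART and CFT-C are delivered in therapy groups and the waitlist is not, yet neither the described mixed-model analysis nor the N = 120 power statement makes a stated allowance for therapy-group clustering

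*Protocol article*

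**What the plan says.** On delivery, the Interventions section states: "Interventions will include ART and CFT-C as group interventions and individual CBT for MDD". Methods/Design adds: "Group therapies will be provided for 18 hours over the course of 8 weeks". Patients are randomised individually to ART, CFT-C or waitlist. Under Recruitment, "10 to 15 individuals at a time will be enrolled in each cohort". The size and number of the therapy groups are not given.

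On sample size, the Participants section sets 120 patients for the group phase (40 per condition) and expects at least 90 to complete individual CBT. It says that the numbers rest on power calculations and that the sample "can be expected to provide sufficient power to detect small effects". No effect size, alpha, power, correlation, ICC or design effect is shown.

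On analysis, the Statistical analyses section states: "Mixed effect modeling will serve as the main approach in the analyses of study data and in the treatment of missing values". Growth curves are computed for each condition over T1-T5 and T6-T10, and the slopes are compared between conditions. The random effects are not listed. The term multilevel appears only for the mediation analysis, without naming the levels.

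**The concern.** Patients in one therapy group share leaders, fellow members and 18 hours of sessions, so their changes in depression may be correlated. The design is therefore partially nested: clustered in ART and CFT-C, and unclustered in the waitlist arm during the group phase. This follows from the stated delivery, whatever the size of the ICC.

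A growth-curve model with patient-level random effects alone handles correlation within a patient over time, but not correlation between patients in the same group. Its intervals for ART vs CFT-C and ART vs waitlist would be too narrow, the first more so because both arms are clustered. ART vs CFT-C is also the comparison meant to remove unspecific factors such as therapeutic alliance. Variation between groups and leaders is one such factor, so a few strong groups could be credited to ART.

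**Working it through.** **The plan's own figure.** The small-effects claim cannot be reproduced uniquely, because no inputs are given. With two-sided alpha 0.05 (assumed) and independent patients:

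- Two-arm comparison of means, 40 per arm, d = 0.2: power is about Φ(0.2/√(2/40) − 1.96) = Φ(−1.07), or 14%. For 80% power, 2 × (2.80/0.2)² gives 393 per arm.
- Three-arm repeated-measures interaction, f = 0.10, N = 120, for a correlation between occasions of 0.5, 0.6 and 0.7: five occasions give 68%, 79% and 91%; four give 61%, 73% and 86%. Table 1 marks the Hamilton scale at four occasions across the whole study.

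The claim is thus reachable only with a repeated-measures calculation and favourable unstated inputs. These variants leave no evident room for clustering.

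**Inputs for the clustering check.**

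- From the article: 120 patients, 40 per arm, cohorts of 10 to 15.
- Assumed: each cohort is split evenly over three arms with one group per active arm. Group size m is then 10/3 = 3.3 to 15/3 = 5, with 120/15 = 8 to 120/10 = 12 groups per active arm.
- Assumed: ICC for slope or change of 0 to 0.15. The article gives no value.

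**Formulas.**

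- Design effect in a grouped arm: DEFF = 1 + (m − 1) × ICC.
- Variance factor: DEFF for ART vs CFT-C; (1 + DEFF)/2 for ART vs waitlist.
- True type I error when group is ignored: 2 × [1 − Φ(1.96/√factor)].
- True standard error relative to the reported one: √factor.

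| m | ICC | DEFF | ART vs CFT-C: type I | SE ratio | ART vs waitlist: type I | SE ratio |
|---|---|---|---|---|---|---|
| any | 0 | 1.00 | 5.0% | 1.00 | 5.0% | 1.00 |
| 3.3 | 0.01 | 1.02 | 5.3% | 1.01 | 5.1% | 1.01 |
| 3.3 | 0.05 | 1.12 | 6.4% | 1.06 | 5.7% | 1.03 |
| 5 | 0.01 | 1.04 | 5.5% | 1.02 | 5.2% | 1.01 |
| 5 | 0.05 | 1.20 | 7.4% | 1.10 | 6.2% | 1.05 |
| 5 | 0.10 | 1.40 | 9.8% | 1.18 | 7.4% | 1.10 |
| 5 | 0.15 | 1.60 | 12.1% | 1.26 | 8.6% | 1.14 |

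A simulation of a t-test that ignores group (40,000 replicates) agrees: at m = 5 and ICC 0.05 it gives 7.7% and 6.2%; at m = 5 and ICC 0.15, 12.3% and 8.8%.

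**Power when group is modelled.** At 40 independent patients per arm, the difference detectable with 80% power is d = 2.80 × √(2/40) = 0.63. For ART vs CFT-C with m = 5, power at that difference falls to 72.5% (ICC 0.05) or 66% (ICC 0.10). The detectable difference rises to 0.63 × √1.2 = 0.69 or 0.63 × √1.4 = 0.74.

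**The case against.** The strongest reply is that the article fixes nothing wrongly here. A mixed model can carry a therapy-group effect, and an article commonly leaves the random-effects structure to the full protocol or analysis plan, which is not shown. The power inputs are not shown either. That stands against the stronger reading a reader might infer: that the model and the power claim treat patients as independent, so that the false-positive rate does exceed 5%. The text says neither. The inflation is conditional on omitting group and on a positive ICC.

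Other points also stand:

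- The cohort of 10 to 15 is an enrolment unit, not a therapy group. Groups of 3 to 5 are an inference, and the ICC is assumed. At ICC 0.01 the inflation is negligible.
- The planned test compares slopes, so the relevant ICC is that of slope or change. A stable difference in level between groups would not inflate slope standard errors in the same way.
- A group effect does not fully capture leaders who run several groups. In T6-T10 all arms receive individual CBT and may share therapists, so waitlist patients may no longer be independent of each other.

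These limits narrow the point but do not remove it. The analysis section is detailed: it names mediation, moderated mediation, latent change and multi-method models. Yet it describes the main comparison without the one dependence between patients that the group delivery creates. The sample-size section makes a positive claim of adequacy that has no visible margin for that dependence.

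**Conclusion.** The point holds in conditional form. The partially nested design is certain from the article, and no allowance for it is stated in the analysis or the power claim. Fitted as described, with no therapy-group term, the model would understate standard errors for any positive group ICC for change. With groups of about 3 to 5 and ICC 0.01 to 0.15, type I error is about 5% to 12% for ART vs CFT-C and 5% to 9% for ART vs waitlist. Both ranges rest on assumed group sizes and ICCs and on a design-effect approximation for a single change score. It is not established that the investigators left group out.

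**What to change.** For the group phase, add a random therapy-group effect on slope or change in ART and CFT-C only, with each waitlist patient as their own cluster. Use small-sample degrees of freedom (Satterthwaite or Kenward-Roger), since there may be only 8 to 12 groups per active arm. For T6-T10, keep the group term and check clustering by individual therapist in all arms. Record a group identifier, and leader and therapist identifiers, for each patient.

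In the Participants section, replace the small-effects wording with a detectable difference at the planned 40 per arm, giving the ICC and group size assumed. No additional patients need be enrolled.

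The cost is a few data columns and a longer model statement, wider intervals (standard error up to about 1.26 times at the top of the assumed range), and a less favourable stated power.

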**Methods/Design:**

In the evaluation of the Affect Regulation Training, we will conduct a prospective randomized-controlled trial. Effects of the Affect Regulation Training on depressive symptom severity and outcomes of subsequent individual therapy for depression will be compared with an active, common factor based treatment and a waitlist control condition. The study sample will include 120 outpatients meeting criteria for Major Depressive Disorder. Depressive symptom severity as assessed by the Hamilton Rating Scale will serve as our primary study outcome. Secondary outcomes will include further indicators of mental health and changes in adaptive emotion regulation skills application. All outcomes will be assessed at intake and at 10 points in time over the course of the 15-month study period. Measures will include self-reports, observer ratings, momentary ecological assessments, and will be complemented in subsamples by experimental investigations and the analysis of hair steroids.

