Despite these encouraging findings, existing research on ART is limited by a number of factors. First, previous clinical studies used a short version of ART. Second, ART has not yet been compared with an untreated control condition or with a condition that accounts for unspecific therapeutic factors. Third, it has not yet been investigated whether ART would augment the effects of other empirically-evidenced treatments for MDD (possibly because enhanced ER skills might allow patients to engage more intensely in the therapeutic process, [31]). Finally, in previous study outcomes the effectiveness of ART was exclusively assessed through self-report measures and only at pre- and post-treatment.

In an attempt to clarify whether experimentally enhancing general ER skills reduces depressive symptom severity and whether fostering adaptive ER skills enhances the outcome of subsequent individual CBT for depression (iCBT-D), we will evaluate the efficacy of ART in a prospective randomized controlled trial. Stand-alone and augmenting effects of ART will be compared with a waitlist control condition and a condition controlling for active ingredients common to most empirically evidenced treatments. Primary (depressive symptom severity) and secondary outcomes will be assessed at intake and 10 points over the course of the study. Measurements will include self-reports, observer ratings, ecological momentary assessments (EMA) [32] and will include experimental investigations and the analysis of hair steroids in subsamples.

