### Primary outcome

The level of depressive symptom severity as assessed by the Hamilton Rating Scale for Depression (HRSD) [42] will serve as the primary study outcome. The HRSD is a clinician-administered semi-structured interview that assesses symptoms of MDD. Based on patients’ responses, clinicians rate the degree of 24 symptoms such as depressed mood, feelings of guilt, sleeping disturbances, and anxiety on 3-point or 5-point Likert scales. Higher sum scores indicate greater symptom severity. The cut-off points of 10, 19, 27, and 35 represent thresholds for mild, moderate, severe, and very severe depression, respectively. The HRSD is sensitive to change and corresponds well with overall clinical ratings of severity [43,44].

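### As printed, the HRSD schedule (T1, T3, T6, T10) does not fit the T1-T5 window: no primary-outcome rating made after the full training enters the stand-alone test of ART

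*Protocol article*

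**What the plan says.** - **Primary outcome.** The Primary outcome section names it: "The level of depressive symptom severity as assessed by the Hamilton Rating Scale for Depression (HRSD". Table 1 labels the row "Depressive symptom severity (primary outcome", instrument "Hamilton rating scale for depression", and marks it at T1, T3, T6 and T10. T0, T2, T4, T5 and T7 to T9 are empty.
- **Meaning of the visits.** The Assessments section sets them as "before (T1), during (T2-4), and after the group-based phase (T5), after the subsequent 4-week follow-up waiting phase before individual CBT starts (T6". T3 is thus the middle one of three visits during the training, T5 is the end-of-training visit, and T6 comes after the wait but before individual CBT.
- **Analysis.** The Statistical analyses section says "Growth curves of ER and depressive symptom severity will be computed per group on the basis of assessments before (T1-T5) and during individual CBT (T6-T10", and gives the purpose as "to test for stand-alone and augmentation effects of ART". The hypothesis is stated on slopes, ART against each control.
- **Visit count.** The Abstract says "All outcomes will be assessed at intake and at 10 points in time". The Background says "Primary (depressive symptom severity) and secondary outcomes will be assessed at intake and 10 points over the course of the study".

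**The concern.** Whether ART lowers depression on its own is one of the trial's two main questions. If the analysis section is followed with the printed Table 1, the primary outcome answers it from ratings made before the training and part-way through it. An effect that is present at the end of the training but only partly developed at T3 would be diluted or missed. The T6 rating, which does follow the full training, serves only as the starting value of the second window. That window is described as during individual CBT, although the Assessments section puts T6 before that therapy begins.

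**Working it through.** **1. HRSD ratings in each window.** The HRSD row has all 11 fields for T0 to T10 and lines up with its neighbours, so a fault in reading the table is unlikely.

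| Window | Stated use | HRSD ratings | BDI-II ratings |
|---|---|---|---|
| T1-T5 | stand-alone | T1, T3 | T1, T2, T3, T4, T5 |
| T6-T10 | augmentation | T6, T10 | T6, T7, T8, T9, T10 |

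With two ratings per window, each HRSD slope is a change score divided by time. Change from T3 to T6, which covers the later part of the training and the 4-week wait, belongs to neither window.

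**2. Comparison with other rows of Table 1.** The Brief Symptom Inventory, the DERS, the informant versions of the scales, and the self-efficacy, perfectionism and self-esteem scales are all marked at T1, T5, T6 and T10. Among instruments that are not given at every visit from T1 on, only the HRSD is marked at T3.

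**3. Visit count.** The Abstract and Background imply intake plus 10 ratings. The HRSD row shows 4, none at intake.

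**4. Illustration of size.** The article gives 120 patients, 40 per condition, and an 8-week group phase. It gives no week for T3, no correlation and no numerical effect size, so its own power statement cannot be recomputed, and nothing here depends on it.

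Assumptions: two arms of 40, two-sided alpha 0.05, SD 1 at each visit, correlation r between visits, and an effect growing linearly to d = 0.5 at week 8.

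- Effect at week w: 0.5 × w/8.
- SE of the between-arm difference in change: √(2 × 2(1 − r)/40). For r = 0.5 this is √0.05 = 0.224; for r = 0.7 it is √0.03 = 0.173.
- Power ≈ Φ(effect/SE − 1.96).

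| Ratings used | Effect | Power, r = 0.5 | Power, r = 0.7 |
|---|---|---|---|
| T1 and T3, T3 at week 2 | 0.125 | 8% | 11% |
| T1 and T3, T3 at week 4 | 0.250 | 20% | 30% |
| T1 and T3, T3 at week 6 | 0.375 | 39% | 58% |
| T1 and T5 (week 8) | 0.500 | 61% | 82% |

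Worked case, T3 at week 4 and r = 0.5: 0.250/0.224 = 1.118; 1.118 − 1.96 = −0.842; Φ = 0.20. At week 8: 0.500/0.224 = 2.236; 2.236 − 1.96 = 0.276; Φ = 0.61.

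The article speaks of small effects. With d = 0.2 at week 8 and T3 at week 4, the same formula gives 7% to 8% from T1 and T3, against 14% to 21% from T1 and T5.

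**The case against.** - **An HRSD rating after the training and before individual CBT does exist, at T6.** This stands. A reader might infer that the trial cannot answer the stand-alone question, or that a null result could not be interpreted. The documents do not support that: the scheduled data can answer it, and the fault lies in where the window is drawn. The BDI-II also covers T1 to T5. It is declared a secondary measure, though, and the article criticises earlier ART studies for relying only on self-report, so it cannot take the place of the HRSD.
- **T3 may simply be a misplaced mark for T5.** The neighbouring rows make this plausible. So it cannot be stated as fact that the test is made on half the training; nor is the week of T3 given. What is certain is that the printed passages conflict.
- **Two ratings do not rule out a mixed model.** Correct. A reader might infer that the planned model cannot be fitted. The article promises mixed models and growth curves per group but never mentions random slopes, and a random-intercept model with a group-by-time term can be estimated from two visits. The sound statement is only that such a slope is a change score.
- **The analysis plan may settle this.** It may, but the point is not an omission. The schedule, the windows and the visit count are all stated here, and they disagree.

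**Conclusion.** The point holds as an internal contradiction about the primary outcome. On the printed schedule and windows, the stand-alone test of the HRSD uses baseline and a mid-training rating, leaves out every rating made after the full training, and leaves the change from T3 to T6 untested. The visit counts in the Abstract and Background are also wrong for the HRSD. None of this rests on an assumption.

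The loss of power does. Under the linear effect reaching d = 0.5, it is 20% to 30% with T3 at week 4, or 8% to 58% over weeks 2 to 6 and r = 0.5 to 0.7, against 61% to 82% with an end-of-training rating. If the effect came early in the training the loss would be smaller; if late, larger. Because T6 is already collected, the harm can be repaired fully in the analysis.

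**What to change.** First establish which HRSD schedule is the real one.

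1. **If T3 is a misprint for T5:** correct Table 1 to T1, T5, T6, T10. The T1-T5 window then contains an end-of-training rating. It still holds only two HRSD values, so describe the test as a change between visits. This is suitable only as a correction of the record: with enrolment in consecutive cohorts, actually moving the interview would leave any cohort already past T5 without the rating.
2. **If T3 is the real schedule:** fit one mixed model to the HRSD over T1, T3, T6 and T10 with visit as a category. Make the difference between ART and each control in change from T1 to T6 the stand-alone test, and change from T6 to T10 the augmentation test. Describe T6 as before individual CBT.
3. **In either case:** keep growth curves for the BDI-II and the ERSQ, which are measured at T1 to T10, and correct the visit counts in the Abstract and Background.

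Option 2 costs a few sentences and no extra interview. Its drawback is that it measures the effect 4 weeks after the training rather than at its end, and this should be said. T6 also ends one contrast and starts the other, so chance error at T6 pushes the two estimates in opposite directions.
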